**Executive summary**

**Title**

Early goal directed therapy for adult bacterial meningitis in Malawi

**Type of research study**

Prospective clinical trial of early goal directed therapy using a before/after design

**Background**

The mortality rate associated with adult bacterial meningitis (ABM) in Malawi is 54% regardless of HIV status and has not been impacted by two adjunctive interventions tested in randomised controlled trials at Queen Elizabeth Central Hospital (dexamethasone and glycerol). A recent study has shown that delays within the medical care in QECH may contribute to this adverse outcome, such as delay to receive antibiotics. By starting a programme of triage, rapid resuscitation and treatment of sick children (ETAT) the overall inpatient mortality rate in acute paediatric admissions at QECH has been reduced from 18% to 9%. This approach, known as resuscitation delivered through early goal directed therapy (EGDT) has shown a relative mortality reduction from adult sepsis in developed countries by 25% (Absolute Reduction 9%), but this has not been tested in adults in Africa. This study seeks to investigate if by utilising existing resources to optimise delivery of standard clinical care interventions using a EGDT, the outcome from ABM can be improved.

**Research question** Can early goal directed resuscitation provided through a bundle of standard interventions have an impact on the clinical management and outcome in acute adult bacterial meningitis (ABM) in Malawi?

**Objectives**

**Broad main objective**

Assessment of the efficacy of early goal directed therapy (EGDT) to deliver target directed resuscitation using a ‘care bundle’ in a resource limited setting for adults with suspected bacterial meningitis

**Specific objectives**

1. To assess the efficacy of each clinical target in the clinical bundle
2. To assess the relative reduction in mortality due to ABM in adults receiving the bundle compared to controls
3. To estimate if the bundle has an impact on the incidence of acute seizures and neurological disability in survivors of ABM
4. To quantify the bacterial load of all patients with *S. pneumoniae* meningitis in blood and CSF, comparing survivors and non-survivors as a marker of poor outcome.
5. To assess inflammatory and immunological biomarkers of severity and outcome in serum and CSF samples to better understand the pathogenesis of adult bacterial meningitis in this context

**Methodology**

1. We will test the bundle in a before/after study with sequentially phased prospective control and intervention groups in the new Anadkat-Wellcome Trust Adult emergency and Trauma Centre (AETC) at Queen Elizabeth Hospital. The bundle will include nurse led rapid assessment and triage and targeted delivery of resuscitation to all subjects with suspected ABM using clear, achievable goal directed targets. Subjects will be excluded retrospectively if an alternative diagnosis is made.
2. The bundle will only include well recognised standard treatments that are already available at QECH, but the targets will ensure these are given promptly and appropriately.

**Expected findings**

We expect that the clinical care of adults with suspected bacterial meningitis will be enhanced using the treatment delivered with EGDT, and the targets will be achievable. We expect this will translate to an improvement in mortality and reduce morbidity in survivors.

**Early goal directed therapy to improve clinical management**

Since a landmark study showing a benefit from targeted resuscitation in sepsis, the concept of using early goal directed therapy (EGDT) with simultaneous interventions (‘sepsis bundle’) has been shown to be highly successful in reducing mortality from bacterial sepsis and septic shock (4). EGDT consists of delivering existing, recognised, evidenced based treatments for a particular condition, in a rapid, protocolised fashion to achieve clinical targets, with the aim to optimise the clinical care available and therefore the outcome.

Estimates of the relative reduction in mortality with EGDT for adult septic shock are between 20-25% (absolute risk reduction 9-10%). The single most effective component has been shown to be early antibiotics (5). Goal directed fluid resuscitation and tissue oxygenation are also critical, forming internationally accepted standards for septic shock management worldwide (6). To be included in a bundle, all EGDT elements must have individual supportive evidence of efficacy and it is expected that the overall bundle, when delivered together, efficacy will be greater than the individual components (7).

**Early goal directed therapy in resource limited settings**

Using EGDT to improve survival is highly applicable to resource limited hospitals. In 2001, the Department of Paediatrics in Queen Elizabeth Central Hospital (QECH) developed Emergency Triage and Treatment (ETAT) in their clinic to prioritise the care of sick children, and have shown an overall reduction in mortality amongst emergency admissions from 18% to 9% (8). Rapid recognition and management of acute illness in adults is part of the 2004 WHO guidelines on the management of unwell adults in resource limited settings ‘Integrated management of adolescent and adult illnesses’ (9). Although neither EGDT nor ETAT are specifically mentioned in this publication, the principles that underline both of these methodologies are recommended. No current publications or registered clinical trials have tested the concept of EGDT in adults in Africa.

**Bacterial load as a marker for mortality in adult meningitis**

High bacterial loads in patients with *S. pneumoniae* sepsis and pneumonia (adults) and meningitis (children) have been correlated with poor outcome, but this has not been studied in ABM (10-11). Bacterial load may prove to be an important contributor to poor outcome in Malawi, and impacted on by early antibiotics. This data may also be important in the further planned laboratory research work, as correlating bacterial load with the degree of immunological response in the CSF may provide novel insights into the pathogenesis of ABM.

This study will test if the concept of EGDT for adults is possible in a resource limited setting, and if it has an impact on outcome. Based on the surviving sepsis campaign bundle (6) and an analysis of the clinical data from MLW/ QEH, this study will test a care bundle, designed to optimise the management of adult meningitis in Malawi, using existing resources in a clinical before/after study.

**Rationale/Justification for the research project**

**Current problems in delivering care for adult meningitis in Blantyre**

The mortality rate for adult bacterial meningitis is very high in resource limited settings, and to date there is no clear explanation for this, or for the failure of adjunctive treatments which have been shown to be effective in other settings. It appears likely from our preliminary studies at QECH that delays in delivering essential care such as antibiotics and intravenous fluids are major contributors to the poor outcome. It is also likely that delays in reaching hospital care also contribute, although this has not been proven.

**Applying EGDT to resource limited settings using existing treatments using targets is potentially achievable and has not been done in adult medicine in Africa**

It is very important to know if deficiencies in the existing healthcare structure contribute to poor outcome and if outcome can be improved by optimising care. By using the early goal directed target (EGDT) approach, we can test if through optimising existing resources and improving clinical care (by shortening assessment times and giving appropriate recognised treatments within a prompt timeframe) is achievable, and if any impact on outcome through this approach is possible.

**Use of the study results**

If the study is successful and the EGDT targets are achievable within the QECH setting, funding and ethical approval will be sought for a much larger cluster randomised study throughout Southern Africa to test the bundle concept definitively.

**Objectives**

**Broad main objective**

Assessment of the efficacy of early goal directed therapy to deliver target directed resuscitation in a resource limited setting for adults with suspected bacterial meningitis using a clinical care bundle.

**Specific objectives**

1. To assess the efficacy of each clinical target in the clinical bundle
2. To assess the relative reduction in mortality due to ABM in adults receiving the bundle compared to controls
3. To estimate if the bundle has an impact on the incidence of acute seizures and neurological disability in survivors of ABM
4. To quantify the bacterial load of all patients with *S. pneumoniae* meningitis in blood and CSF, comparing survivors and non-survivors as a marker of poor outcome.
5. To assess inflammatory and immunological biomarkers of severity and outcome in serum and CSF samples to better understand the pathogenesis of adult bacterial meningitis in this context

**Methodology**

1. **Study design**

The study is a single site, clinical prospective observational study with a before/after design, which is the only feasible study design with the current constraints of ethics, time and funding. A traditional randomised controlled design is not appropriate for this intervention. Each element of the clinical care bundle has evidence to support its use and forms part of standard care. Therefore it is unethical to randomise half of the study population not to receive good quality medical care. However a prospective control population is needed as the potential additional benefit to participants of admission through the AETC is not yet quantified, compared to admission directly through the medical ward. The only alternative to a parallel design for a complex intervention is a before/after where the benefit of the intervention can be assessed in the after group, compared to the control before group. There are several problems with this design, mainly due to several confounders including time and staff. The ideal design for this study is a cluster randomised study, where the intervention would be tested in several centres, and outcomes compared to control centres without the intervention. This is the only study design that can give definitive statistical evidence of efficacy of EDGT. However this type of study is large and time consuming and beyond the scope of this fellowship. Should the EGDT intervention prove successful in this study it will act as a pilot for a cluster randomised study to be performed throughout Southern Africa.

The before/after design is the most common for studies testing EGDT in sepsis, as it is the only methodology that can be used in a single site. In 9 studies of EGDT summarised in a recent systematic review, 8 were single site before/after and one was a cluster randomised design over multiple sites (4-5).

The Medical Research Council guidelines on trial design for complex interventions, endorse the before/after design where a group of interventions are given together in a single site and every attempt is made to minimise any aspects of study delivery and design that may lead to confounding (21).

This before/after study is divided into two consecutive phases, the ‘before’ group named phase 1(observational controls) and the ‘after’ group, phase 2 (implementation of bundle). Phase 2b will start at the same time point as phase 1, but one year later to minimise the effect of seasonal variation in the presentation of ABM.

All adults admitted to AETC in both phases with suspected ABM will be screened and included using identical inclusion criteria to ensure the participants in both phases are as similar as possible.

To minimise confounding, active recruitment, prospective data collection and follow up of all study subjects will be identical in both phases.

Phase 2 is divided into 2a, a short pilot phase to introduce each bundle element sequentially and phase 2b, the active bundle. This is due to the complexity of the care bundle to ensure that all study team members are familiar with each target and intervention before full active data collection starts in Phase 2b. Multiple studies of care bundles in different settings have documented the failure of implementation of a bundle if it is not piloted first and all study staff are trained fully in the bundle delivery (22-23).

1. **Study place**

This study will be based entirely in the new Anadkat-Wellcome Trust Adult Emergency Trauma Centre (AETC) which is was completed in September 2011 and became operational in October2011 and Queen Elizabeth Central Hospital, Blantyre, Malawi

1. **Study population**

Adults (aged 14 or over) presenting to the AETC with suspected bacterial meningitis

**Inclusion criteria**

- Adults ≥14 years age
- Fever/history of fever plus one of:

1. Coma
2. Severe Headache
3. Nuchal rigidity
4. Seizures
5. Confusion

The diagnosis of ABM will be based at presentation on clinical symptoms and signs. A formal diagnosis of ABM will be made following CSF analysis using the following criteria: ***CSF WCC >50 cells/mm^2^ (predominantly neutrophils), visible bacterial seen in the counting chamber irrespective of cell count***, ***positive Gram’s stain*** or culture/PCR positivity for any bacteria known to cause meningitis.

**Exclusion criteria**

Immediate

- Pre-admission diagnosed terminal illness (e.g. metastatic malignancy)

LP results

- CSF positive on microscopy, culture or antibody testing for an organism known to cause chronic meningitis (fungal/tuberculosis/parasitic etc.)
- CSF that is culture/microscopy/PCR negative, but the CSF WCC is greater than 80% lymphocytes and no pre-admission antibiotics have been given

Subjects with non-inflammatory ***CSF < 50 WBCs*** and culture/gram/PCR negative will be excluded from the main ABM analysis, but will be analysed as a separate group.

Patients presenting in-extremis or with symptoms or signs suggesting death within 4-6 hours will be included in the analysis, but also subjected to a separate sub analysis.

**Control group**

Phase 1 will consist entirely of recruitment of controls for the ‘before’ phase 1 of the study design. All aspects of recruitment and the consent process will be identical to the intervention ‘after’ phase 2. No EGDT will be given to the controls, and their clinical management will be determined by the treating clinician and delivered by the study nurses. Regular observations will be performed and charted by the study nurses for each subject for the 6 hour study period.

**Intervention group**

Phase 2 will consist entirely of recruitment of subjects to be given the care bundle intervention. All other aspects of recruitment consent and observation will be identical to phase 1.

1. **Detailed Methodology**

**iv. i Intervention design**

EGDT will be delivered using a clinical care bundle, based on the ‘ABCD’ approach to resuscitation which has been developed and validated by the American and UK resuscitation councils (24) and consists of eight components, all of which are currently available in QECH and all of which are recognised existing clinical treatments which have supportive evidence of efficacy. The individual components of the bundle can be seen in table 1.

Staff training will form an important component of bundle delivery during phase 2a and ongoing through phase 2b, but will not form a specific bundle element. This is due to difficulties in assessing staff training when no formalised resuscitation training is available that is appropriate to resource limited settings.

The duration of the intervention will be 6 hours from initial screening to the point at which attempts to meet all targets have been achieved. Each subject will receive hourly observations including GCS scoring, blood pressure and pulse measurements. A lumbar puncture for the diagnosis of ABM will be performed at the earliest opportunity.

Study nurses and a clinical officer will deliver the bundle following training, using defined targets (table 2) within the AETC. At the end of the 6 hour study period, the bundle will stop, and the subject will be transferred to the medical ward for ongoing routine care. A flowchart of the study process is available in the appendix 9.

***Table 1 – Bundle components***

| **Bundle components** |
| --- |
| Naso-pharyngeal airway if GCS <8  Head up/bed tilt 30° if GCS <11  IV access, 2g Ceftriaxone stat  Oxygen via concentrator if SpO2 <93%  IV fluid (Ringer’s Lactate) bolus 20ml/kg if clinical shock, 125ml/hr if no clinical shock (table 3)  Transfusion of packed red cells if haemoglobin <6.0g/dL  Correction of hypoglycaemia with oral dextrose and drinks/food if GCS >11, or with iv dextrose 10-50% via a bolus/infusion if GCS <11  Prompt treatment seizures  *(IV diazepam/lorazepam plus phenytoin for persistent fits/status epilepticus)* |

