***Table 2 – Goal directed targets***

| **Parameter** | **Target** | **Intervention** | **Test of intervention** |
| --- | --- | --- | --- |
| Timing of clinical assessment | Medical review <1 hour of arrival | Training in recognition of the symptoms and signs of meningitis and rapid triage | Timed and signed flow chart |
| Antibiotic therapy | 1^st^ dose within 1 hour of arrival | Education of importance of antibiotics, sepsis flow chart | Timed drug chart |
| Glucose | BM >4 | S/L , NG or IV dextrose | Repeat BM |
| Oxygenation | Sp02 >94% | Nasal flow 02 from concentrator  Packed red cell Transfusion if significant anaemia (Hb 6.0g/dL) | Regular Sp02 monitoring |
| Perfusion | CRT<2 sec, BP >90 syst, MAP >70, no postural hypotension (lying-sitting)/  UOP>0.5ml/kg (if catheterised | IV fluid bolus 20ml/kg Ringer’s lactate where available. | Repeated fluid balance assessment at 1hour then repeated |
| Seizures | No seizures | Acute prompt treatment of seizures with IV/PR benzodiazepines and IV phenytoin if seizures persist | Seizure chart |

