***Table 3- Definition of clinical shock***

| **General variables** | **Hemodynamic variables** | **Organ dysfunction variables** | **Tissue perfusion variables** |
| --- | --- | --- | --- |
| Heart rate >90 bpm | Arterial hypotension (SBP <90 mm Hg | Acute oliguria (urine output <0.5 mL/Kg/hr **or** <45 ml/hr for at least 2 hrs (if catheterised)/ no urine production for 12 hours despite adequate fluid resuscitation) | Decreased capillary refill (>3 seconds) |
| Tachypnea RR>25 | MAP <70 mm Hg | Ileus (absent bowel sounds) | Skin mottling |
| Altered mental status | SBP decrease >40 mm Hg |  |  |

All interventions are part of routine accepted care for critically ill patients at QECH, however they are incompletely implemented and are currently not target driven.

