**iv.ii Endpoints**

***Primary***

Proportion of each clinical target achieved by the bundle

Total proportion clinical targets when combined together, achieved by the bundle

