**Target and bundle sustainability related data**

Data will be collected on a weekly basis by the nurses through feedback to the PI to assess if the AETC staffing and equipment levels would be appropriate to deliver targeted care. An assessment will be made with the assistance of a local health economist of the additional cost of implementing each element of the bundle (if proven to be effective) into long term practice.

1. **Data analysis**

Each element of the bundle will be analysed separately to calculate the percentage of each clinical target was achieved.

Analysis will be primarily by intention to treat, and then per-protocol. Data will be collected using ‘redcap’ electronically and then transferred to SPSS/PASW statistical programme and GraphPad5™ software for analysis.

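### The bundle components and triggers (Tables 1 and 3) do not line up with the scored targets (Table 2): two components have no target to be analysed through, and some subjects can miss a target without meeting the trigger

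*Protocol*

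**What the plan says.** Protocol section iv.ii gives the primary endpoint in two parts: "Proportion of each clinical target achieved by the bundle" and "Total proportion clinical targets when combined together, achieved by the bundle". The Data analysis section then says: "Each element of the bundle will be analysed separately to calculate the percentage of each clinical target was achieved".

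Section iv.i says the bundle "consists of eight components, all of which are currently available in QECH". Table 1 lists these components, most of them with the condition that triggers them. The same section has study staff deliver the bundle using the targets of Table 2. Three thresholds matter here:

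- Oxygen: Table 1 has "Oxygen via concentrator if SpO2 <93" (percent); the Table 2 target is a saturation above 94%.
- Perfusion: the Table 2 target begins "CRT<2 sec, BP >90 syst, MAP >70", followed by postural hypotension and urine output.
- Fluid: Table 1 gives a bolus if there is clinical shock as defined in Table 3, and maintenance fluid otherwise. Table 3 lists among its signs "Decreased capillary refill (>3 seconds" (bracket left open in the quote).

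**The concern.** Target achievement is the primary endpoint, and the Data analysis section compares it between the two phases. Under the heading Use of the study results, achievable targets are a condition for seeking a larger cluster randomised study. The score should therefore separate two things: whether staff delivered the bundle, and whether the tables agree with each other on when to act.

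As written it may not. An element without a target cannot be analysed as promised. A subject whose reading lies between the trigger and the target can be scored as a miss although Table 1 did not call for the oxygen or the bolus. Staff who work from Table 1 and staff who work from Table 2 could also treat that subject differently.

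**Working it through.** **Inputs.** Tables 1, 2 and 3 (section iv.i); the primary endpoint (section iv.ii); planned recruitment of 200-250 in total, split equally between phases (Sample size).

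**Step 1: count and match.** Table 1 has 8 entries, which reproduces the figure in section iv.i ("consists of eight components"). Table 2 has 6 parameters.

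| Table 1 component | Table 2 row |
| --- | --- |
| Naso-pharyngeal airway | none |
| Head-up tilt | none |
| IV access and ceftriaxone | Antibiotic therapy |
| Oxygen | Oxygenation |
| IV fluid | Perfusion |
| Transfusion | listed as an intervention under Oxygenation; target and test are SpO2 |
| Correction of hypoglycaemia | Glucose |
| Seizure treatment | Seizures |

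Components with no row: 2/8 = 25%. Components with no target of their own, adding transfusion: 3/8 = 37.5%. The sixth Table 2 row, medical review within an hour, has no Table 1 entry.

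**Step 2: readings that miss the target without meeting the trigger.**

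- SpO2: not below 93 and not above 94 leaves the whole-number readings 93% and 94%.
- Capillary refill: not above 3 s and not below 2 s leaves 2 to 3 s inclusive.
- Systolic pressure of exactly 90 and mean arterial pressure of exactly 70 also fall between Table 3 (below) and Table 2 (above), but these are single points.
- Postural hypotension fails the Table 2 target and is not among the Table 3 signs.

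For oxygen, Table 1 calls for nothing in this band. For capillary refill with no other shock sign, Table 1 gives maintenance fluid but no bolus.

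**Step 3: size.** Per phase, n = 200/2 = 100 to 250/2 = 125. Let x be the share of subjects in such a band for one target. The Protocol does not give x, so the values below are assumptions. If all subjects are in the denominator and their readings stay in the band, misses with no trigger met = x × n, and the highest attainable proportion on that target = 1 − x.

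| x (assumed) | Misses per phase, n = 100 | n = 125 | Ceiling on that target |
| --- | --- | --- | --- |
| 5% | 5 | 6.25 | 95% |
| 10% | 10 | 12.5 | 90% |
| 20% | 20 | 25 | 80% |

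If only triggered subjects are in the denominator, this effect disappears. The Protocol does not say which applies.

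**Step 4: Table 3.** It has four columns of variables and no statement of how many, or which, make up clinical shock. One variable is altered mental status; coma and confusion are both qualifying inclusion criteria. Table 1 uses Table 3 to choose between bolus and maintenance fluid, and the evidence summary for the bundle also treats shocked and non-shocked adults differently. Two careful readers could therefore classify the same subject differently. The Burden and risks section lists excess fluid as a potential harm.

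**The case against.** The strongest reply is that the primary endpoint is worded by target. All six Table 2 rows have a target and a test, so the endpoint can be tabulated. This stands. A reader might infer from the missing rows that the primary endpoint cannot be computed, but section iv.ii does not support that. What cannot be delivered is the element-level result in the Data analysis section, for airway and tilt, and for transfusion in its own right.

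Second, a threshold for starting treatment may legitimately differ from the goal of treatment, and the Protocol gives a source for its 93% figure. This also stands: the difference alone is not an error, and trigger and target need not be equal. The difficulty is that nothing says how subjects between the two are scored.

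Third, Table 2 has its own intervention column, so it can be read as calling for oxygen or a bolus whenever its target is missed. On that reading the band is not empty of action, but the reading conflicts with the conditions in Tables 1 and 3, so the ambiguity over when to act remains.

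Fourth, the denominator and the reading that counts may be set in a statistical analysis plan that is not shown. That is fair, and their absence is not the point. Such a plan cannot, however, settle which table staff follow or how shock is defined.

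Fifth, the executive summary places rapid assessment and triage within the bundle, so medical review is not a foreign target; it is only absent from Table 1. Transfusion is justified in the Protocol by oxygen delivery to tissues, so its place in the oxygenation row looks deliberate. The strict count of components with no row is 2 of 8.

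**Conclusion.** The point holds in limited form. Two of eight components (25%) have no target through which the promised element analysis could run, and a third, transfusion, is tested only by saturation. The oxygen and capillary refill thresholds leave bands of 93-94% and 2-3 s in which a target is missed with no trigger met. Such subjects count as failures under perfect delivery only if every subject is in the denominator and the readings stay in the band. The ceilings of 95%, 90% and 80% rest on assumed shares and show scale only.

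A reader might also infer that most confused or comatose subjects would be handled as shocked. That requires an any-one-variable reading of Table 3, which the Protocol never states. What the text supports is that the classification is open to different readings.

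**What to change.** 1. Reconcile Tables 1, 2 and 3 before Phase 2a. The clinical lead decides the thresholds and how the Table 3 variables combine; this review takes no view on either.
2. Either restate the Data analysis sentence as analysis of the six Table 2 targets, or add delivered/not-delivered scoring for airway, tilt and transfusion.
3. For the primary endpoint, report subjects who miss a target without meeting the Table 1 or Table 3 trigger as a separate not-triggered category, by the same rule in both phases, and not as failures of bundle delivery. A subject who met the trigger and then fell short of the target remains a miss.

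The cost is edits to the tables and wording. The delivered/not-delivered option has a small further cost: delivery must be charted in both phases, so that charting has to be in place from the start of Phase 1.
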